#### Client experiences of SEE 2.0

Qualitative interviews will be conducted with clients receiving SEE 2.0 to explore their experiences with the SEE intervention process and its influence on self-management, everyday life and health. A purposeful selection of a heterogeneous sample^60^ of 6–12 clients will take place until saturation^61^ in the data is reached. Clients will be interviewed on two occasions: 1 month into the programme and after completion (4–5 months after the start). The qualitative, open, in-depth interviews^62^ will include questions addressing the clients’ experiences of how they are developing self-management during the intervention process and its meaning for activities in everyday life. The participants’ experience of whether the change process evolves, as well as their learning and adoption of self-analysis and management strategies, will also be a focus.

#### Intervention adherence

To detect adherence to SEE’s intervention process and guide (2.0), a study-specific registration form will be used for structured interviews with OTs at two points: when phase 4 is completed and when the intervention is completed. In addition, researchers will take continuous field notes on aspects of feasibility, including the adherence and implementation observed during meetings with participants (both clients and OTs).

#### OTs’ experiences with SEE 2.0

FG discussions with periodic recurring discussions^63 64^ will take place with the OTs who deliver SEE 2.0 during the study period. The key questions in the discussions will focus on the feasibility, acceptability, value and implementation of SEE, including how the educational programme and the intervention guide support the delivery of the programme.

#### Professionals’ experiences with SEE 2.0

FG discussions^63 64^ will be conducted with various groups of participants who have used SEE to explore the feasibility and implementation of SEE 2.0. The FGs will take place in 2–4 groups with 3–5 participants each to collect data on SEE feasibility, acceptability, value and implementation. The key questions will also focus on opportunities and obstacles for integrating SEE into various healthcare settings, referral processes and different care pathways, as well as the potential of transferability to other contexts.

### Data management

Data will be stored securely with limited access in accordance with regulations and guidelines, as described in the data management plan. Participants will be assigned a code number, which will be used to pseudonymise all the research data. The list of participants’ code numbers will be stored securely in a locked cabinet, separately from the data and consent forms. The data from the assessments and study-specific forms will be transferred to a computer file for calculation. The qualitative interviews and FGs will be recorded on an audio file and subsequently transcribed pseudonymically to word files. Creation of the files will involve processes to check and promote data quality. When the data are transferred to computer files, access will require multifactor authentication with passwords. The data will be stored on LTUdrive, a storage service provided by Luleå University of Technology (LTU) in Sweden. This service meets the requirements for secure data storage, sharing and protection in accordance with research ethics and the General Data Protection Regulation (GDPR).^65^ After the project is completed, read-me files that enable the reuse of data, along with all related materials, will be securely stored long-term in the central archive at LTU.

### Data analysis

The statistical analysis will assess the suitability of the assessments in detecting outcomes of SEE 2.0 at 4 and 12 months after entry into the programme. In this study, descriptive statistics and non-parametric tests will be used to identify patterns of changes and compare outcomes on respective outcome assessments over time, from baseline to 4 and 12 months. The intention-to-treat approach will be applied, and per-protocol analyses will be conducted if necessary. A gender perspective will be considered in the data analysis to identify potential differences and similarities in outcomes. Sociodemographic characteristics in relation to outcomes will be analysed descriptively. The significance level will be set at p<0.05 for all the statistical tests. All the data from the enrolment process, the number of complete or incomplete assessments, study-specific forms for adherence, acceptability, value, potential harms and field notes will be compiled descriptively^38 66^ by analysis of content and descriptive statistics. The qualitative interviews with the clients will be analysed using the constant comparative method of grounded theory,^61^ as this method is suitable for identifying patterns in interactions, strategies and processes such as intervention processes. The FG discussions will be analysed with FG analysis^63 64^ to identify themes in the collective experiences.

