**Trial registration number:**

NCT06484322.

STRENGTHS AND LIMITATIONS OF THIS STUDYThe intervention will leverage therapeutic mechanisms of the internet-based format to promote clients’ development of self-management in activities of everyday life.The combination of quantitative and qualitative data will provide a comprehensive assessment of the feasibility of the intervention and the study design.This study adopts a pragmatic approach, which, while challenging, will enhance the clinical applicability of the results.The small study sample without a control group will limit the ability to generalise potential effects.

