
### Objectives

The project aims to evaluate the feasibility and implementation potential of SEE 2.0 for people with long-term health conditions across selected primary care and hospital-based services in Sweden. The following objectives were defined to assess SEE 2.0 and the study design:

Evaluate participant recruitment and retention.Evaluate the assessments’ suitability to detect outcomes of SEE at 4 and 12 months after entry into the programme, as well as the acceptability of the assessments.Evaluate client participants’ acceptability and value of SEE.Explore client participants’ experiences with the SEE intervention process and its influence on their self-management, everyday life and health.Evaluate participant (client and OT) adherence to SEE.Explore OTs’ and managers’ experiences of feasibility, acceptability, value and implementation potential of deliver SEE across different healthcare settings.

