## Methods and analysis

### Design

This feasibility study of SEE 2.0 uses a pretest and post-test design with no control group, embedded within a mixed-method approach.^3336^,^40^ The data collection comprises outcome assessments, qualitative semistructured interviews, focus group (FG) discussions and study-specific forms for descriptive data. The study adheres to the Medical Research Council guidelines^33 41 42^ for evaluating complex interventions, and the feasibility study protocol follows the ‘Standard Protocol Items: Recommendations for Intervention Trials’.^43 44^ The trial is registered at ClinicalTrials.gov (ID: NCT06484322). A logical model^45^ provides a simplified overview of how SEE, including its components, is designed and expected to work (online supplemental table S1).

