#### Suitability and acceptability of outcome assessments

To evaluate the assessments’ suitability for detecting the outcomes of SEE 2.0 and their acceptability, responses to the assessments and complete and incomplete assessments, including missing values, will be registered. The primary outcome is engagement in activities, and potential improvements will be assessed from different perspectives. Satisfaction with Daily Occupations-Occupational Balance (SDO-OB)^47 48^ is an interview-based questionnaire that, in 13 items, addresses the activity level (ranging from 0 to 13), satisfaction with daily activities (ranging from 13 to 91) and general balance in activities from a time allocation perspective (five response alternatives ranging from −2 to +2). The Occupational Balance Questionnaire (OBQ-11)^49^ is a self-report questionnaire assessing balance in activities consisting of 11 items, each rated on a 4-point Likert scale. The scores are summed to yield a total score ranging from 0 to 33 points. The Occupational Value Assessment with Predefined items (Oval-pd)^50 51^ is a self-report questionnaire that assesses the perception of occupational value. The Oval-pd includes 18 items rated on a 4-point Likert scale, with total scores ranging from 18 to 72.

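### An uncontrolled pre-post test at p<0.05 in 30–40 clients cannot show whether an assessment is suitable to detect outcomes of SEE (Objective 2)

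*Protocol article*

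**What the plan says.** Objective 2 is worded as follows, with its last two words left off: "Evaluate the assessments’ suitability to detect outcomes of SEE at 4 and 12 months after entry into the programme, as well as the acceptability of". The Data analysis section gives this task to the statistics: "The statistical analysis will assess the suitability of the assessments in detecting outcomes of SEE 2.0 at 4 and 12 months". The method is described thus: "descriptive statistics and non-parametric tests will be used to identify patterns of changes and compare outcomes on respective outcome assessments over time". Each follow-up is compared with the start, and the threshold is given as "The significance level will be set at p<0.05 for all the statistical tests". On the analysis set it says "The intention-to-treat approach will be applied, and per-protocol analyses will be conducted if necessary".

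The Design section says the study "uses a pretest and post-test design with no control group, embedded within a mixed-method approach". The Intervention section adds that clients receive usual care when needed. The Sample size section sets 30–40 clients without a formal calculation.

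The tests are not the only evidence for Objective 2. The section on suitability and acceptability of outcome assessments also records responses, complete and incomplete assessments and missing values, and the Data analysis section summarises completeness descriptively. The primary outcome is a domain measured by several scores: "The primary outcome is engagement in activities, and potential improvements will be assessed from different perspectives".

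**The concern.** Suitability to detect outcomes is a property of the instrument: does its score move when the client's situation moves, and does it have room to do so? The p-value of a one-group change mixes that property with four other things: how much clients truly changed, how many were measured, what would have happened without SEE, and regression to the mean.

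Background change is plausible here. The Introduction describes unpredictable and fluctuating symptoms, clients enter when they express a need for change, and usual care runs alongside. A significant result is therefore not evidence that a scale picks up outcomes of SEE. A non-significant result cannot separate an insensitive scale from no true change or too few clients.

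The results are meant to guide whether and how a full-scale evaluation is planned. If the significance pattern informs the choice of instruments, a responsive scale could look unsuitable because of sample size, and a scale that only follows background change could look suitable.

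**Working it through.** The article gives no number of tests and no power figure, so there is nothing of its own to reproduce.

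**1. Number of scores** (from the section on suitability and acceptability of outcome assessments)

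- Primary domain: SDO-OB 3, OBQ-11 1, Oval-pd 1 = 5.
- Secondary: WAI 1–3 (ability rating, with or without the two demand ratings), work ability and sick leave question 1–2, LiSat-11 items 3, EQ VAS 1, RAND-36 8, GSE-10 1, PSS-10 1, MFS 1 = 17–20.
- Total: 22–25 scores. With two contrasts each (baseline to 4 months, baseline to 12 months): 44–50 tests. One overall three-timepoint test per score would give 22–25.

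**2. False positives if nothing changes**

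- Expected number: 44 × 0.05 = 2.2; 50 × 0.05 = 2.5.
- Chance of at least one, independent tests: 1 − 0.95^44 = 0.90; 1 − 0.95^50 = 0.92.
- The scores are correlated, so this is an upper figure. For 50 tests, simulation gives 0.82, 0.69 and 0.51 at assumed between-score correlations of 0.3, 0.5 and 0.7 (correlation between visits 0.5).

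**3. How often one test is significant** (simulated Wilcoxon signed-rank test, normal changes, two-sided 0.05, everyone followed up)

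| Assumed standardised change | n = 30 | n = 40 |
|---|---|---|
| 0 | 5% | 5% |
| 0.3 | 34% | 43–44% |
| 0.5 | 74% | 85% |

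The 43–44% is the range over simulation runs. The table reads the same whether the change comes from SEE or from natural course, usual care or regression to the mean. The test cannot tell these apart.

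**4. Change detectable with 80% power**

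(1.96 + 0.84) / √(n × 0.955), where 0.955 is the efficiency of the signed-rank test relative to the t-test under normality:

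- n = 30: 2.80 / √28.65 = 0.52
- n = 40: 2.80 / √38.2 = 0.45

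A scale whose clients truly changed by less than about half a standard deviation of change would often look unsuitable.

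**5. What an interval would show instead**

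The standard error of a standardised response mean (SRM) is about √(1/n + SRM²/(2n)). For an observed SRM of 0.3:

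- n = 30: √(0.0333 + 0.0015) = 0.19; 95% CI 0.3 ± 1.96 × 0.187 = −0.07 to 0.67
- n = 40: √(0.0250 + 0.0011) = 0.16; 95% CI 0.3 ± 1.96 × 0.162 = −0.02 to 0.62

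Both results would be called non-significant. The interval shows what that label hides: the data are compatible with almost no movement and with a substantial one.

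**The case against.** The strongest reply is that the article never says an assessment is suitable if p<0.05. It sets a significance level for tests, names descriptive statistics first, and uses completeness and missing values as well. This stands. A reader might infer that Objective 2 rests on the tests alone, or that instruments will be kept or dropped by significance. The text contains no such rule. What remains is that the task is given to the statistical analysis, and the only inferential threshold offered for it cannot do that task.

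A reader might also infer that the tests will use only clients with follow-up, so that the analysis breaks the intention-to-treat promise. The documents do not support this. No specific test and no missing-data method is named, and the rules for missing follow-up and for the per-protocol set may sit in a fuller plan that is not shown. It can only be said that a complete-pair test would not by itself deliver intention-to-treat, so the set should be described. No dropout rate is given either, so any figure for bias from attrition would follow from assumptions alone.

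The multiplicity figures carry limited weight. The study makes no confirmatory claim, the count depends on two contrasts per score, and the chance of any false positive depends strongly on correlation.

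The strengths and limitations box says "The small study sample without a control group will limit the ability to generalise potential effects". One might read this as an error, since a missing control limits attribution before generalisation. It is a matter of wording: the limitation is disclosed, and no analysis depends on it.

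Finally, a single-group standardised response mean carries the same background change as the p-value. That is true, so it must be read as observed change. It still separates size from precision, which a p-value does not.

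**Conclusion.** The concern holds in a limited form. In one group of 30–40 clients with usual care alongside, p<0.05 on pre-post change cannot establish that an assessment is suitable to detect outcomes of SEE, in either direction. With an assumed standardised change of 0.3, the test is significant in about 34% of studies at n = 30 and 43–44% at n = 40, whatever the cause of the change. These figures assume normal changes and full follow-up; the 0.3 is illustrative and not taken from the article. The 44–50 tests, with 2.2–2.5 expected false positives under no change, are a secondary point. This is an inexpensive improvement to how Objective 2 is answered. It does not show that the study is invalid or that its intention-to-treat statement is false.

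**What to change.** In the Data analysis section:

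- State that suitability of the assessments will not be judged by p<0.05, and that any p-values are exploratory.
- For each score at 4 and 12 months, report the standardised response mean with 95% confidence interval, the percentage of clients at floor and at ceiling, and completeness.
- State that observed change cannot be attributed to SEE without a control group, and that the standardised response mean is read as observed change, not as an effect.
- Describe the analysis set as all included clients regardless of adherence, and give the number contributing at each visit.
- Where feasible, relate 4-month change to the client-rated value form already mailed at that visit (section on acceptability and value of SEE 2.0). Note that it rates the value of SEE and not change in each construct, and is collected only at 4 months. This step is optional.

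The cost is a few sentences and a little more analysis on data already being collected. The downside is that there will be no significance claims to report.

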## Patient and public involvement

The intervention programme SEE is developed together with users based on their needs,^4^ with their perspective being central. SEE is designed to meet clients’ need for support in developing self-management strategies to manage activities of everyday life by improving access to care through person-centred internet-based interventions. The choice of outcome assessments is informed by their priorities. SEE has thus far been evaluated with contributions from users and other concerned parties.^27^,^2931 32^ This protocol is also designed to incorporate the experiences of clients, OTs, managers and other staff. Researchers will consistently update users on the project’s progress and actively involve them in discussions about various research steps and dissemination methods.

## Ethics and dissemination

The project has been approved by the Swedish Ethical Review Authority (EPM Dnr: 2023-08032-01, 2024-042277-02, 2025-00635-02, 2025-04193-02) and will be conducted in accordance with the Declaration of Helsinki,^67^ the Swedish law of ethical research on humans^68^ and the GDPR.^65^ All participants will receive information about what participation in the research means both orally and in writing and can ask questions before they sign the written informed consent form and send it to the researchers. This includes information about the potential benefits or risks of participation and the right to withdraw their participation in the study at any time without explanation. They will also be informed that the data will be treated as confidential. Given the small sample size from a local perspective, the amount of personal information will be limited to ensure that participants’ identities cannot be derived from study presentations as in scientific papers.

During the implementation of the internet-based intervention SEE 2.0, patient safety and the protection of sensitive data are ensured by using the support and treatment platform on Sweden’s 1177 National Healthcare Guide. Logging in to the platform is performed via national e-identification. Based on person-centredness, clients can choose whether to carry out the guiding dialogues that support their change process digitally or via personal meetings at the healthcare settings. For digital meetings, secure forums recommended by the organisation will be used. The researchers will not have access to 1177 or medical records.

The results will be presented at conferences that attract researchers, professionals and the general public. Particular emphasis will be placed on reaching out to interest groups (such as patient and professional associations). The studies will be published in international scientific journals, and the researchers will adhere to established authorship guidelines. Popular science summaries of the results will also be created for various audiences and shared on the LTU website and social media.

## Discussion

This study aims to further assess both SEE 2.0 and the study design to determine the feasibility prior to proceeding to a full-scale evaluation in the next step of our research. A major strength of the design is that it is informed by results from our previous research,^27 28 31^ addressing remaining uncertainties about programme feasibility and by our original intentions^4^ to evaluate the use of SEE in a broader client population and at various levels of care. Another advantage is its pragmatic approach,^69^ with SEE being delivered by OTs in various standard healthcare settings. The inclusion criteria for clients are broad enough to reflect the typical pool of clients with limitations in activities of everyday life. Additionally, multiple healthcare settings are involved in recruiting clients to ensure the representation of individuals with different diagnoses from both rural and urban areas with diverse socioeconomic backgrounds. At the same time, a potential limitation is that delivering interventions in standard healthcare settings may be influenced by organisational changes and adherence difficulties to the delivery of the programme. These factors could affect the consistency of implementation. However, such challenges also provide valuable information on the feasibility, acceptability and implementation of SEE in routine practice from the perspectives of different user groups. Furthermore, this pragmatic approach increases the clinical applicability of the results across different user groups and settings, while highlighting the adjustments needed to improve both the intervention and the study design.

Another strength of SEE 2.0 is its innovative character. It is unique in that it is not standard practice to deliver complete occupational therapy intervention processes via the web, and currently no other occupational therapy intervention is available through Sweden’s National Healthcare Platform. Thus, the development and testing of SEE represent an important contribution to the digitalisation of occupational therapy. A further advantage is that the internet-based format improves access to person-centred support and empowers clients, which may lead to more sustainable health outcomes over time. By including the flipped classroom approach^70^ in the programme theory,^4 30^ SEE also introduces therapeutic mechanisms that are not available in traditional in-place rehabilitation.^28^ A possible limitation, however, is that digital delivery may not suit all clients, particularly those with limited digital literacy, cognitive challenges or poor access to technology. Conversely, it may be particularly suitable for clients living at a distance from care facilities or with reduced capacity to travel. SEE’s internet-based format, which combines clients’ own preparation work with guided dialogues with an OT, is designed to improve clients’ self-management and promote sustainable health outcomes. A strength of this approach is that it fosters self-analysis and activity-focused management strategies, supporting a healthy balance of engagement in everyday activities when capacity changes. The knowledge gained will inform the design of future internet-based interventions and their implementation in practice.
